## Abstract

**Background:**

Systematic treatment of all individuals living in the same compound of a clinical malaria case may clear asymptomatic infections and possibly reduce malaria transmission, where this is focal. High and sustained coverage is extremely important and requires active community engagement. This study explores a community-based approach to treating malaria case contacts.

**Methods/design:**

This is a cluster-randomized trial to determine whether, in low-transmission areas, treating individuals living in the same compound of a clinical malaria case with dihydroartemisinin-piperaquine can reduce parasite carriage and thus residual malaria transmission. Treatment will be administered through the local health system with the approach of encouraging community participation designed and monitored through formative research. The trial goal is to show that this approach can reduce in intervention villages the prevalence of *Plasmodium falciparum* infection toward the end of the malaria transmission season.

**Discussion:**

Adherence and cooperation of the local communities are critical for the success of mass treatment campaigns aimed at reducing malaria transmission. By exploring community perceptions of the changing trends in malaria burden, existing health systems, and reaction to self-administered treatment, this study will develop and adapt a model for community engagement toward malaria elimination that is cost-effective and fits within the existing health system.

**Trial registration:**

Clinical trials.gov, NCT02878200. Registered on 25 August 2016.

**Electronic supplementary material:**

The online version of this article (10.1186/s13063-018-2506-x) contains supplementary material, which is available to authorized users.

## Background

There is growing interest in mass drug administration (MDA) of at-risk populations with an effective antimalarial as a means to reduce the human reservoir of infection [1]. MDA aims to provide full treatment courses to the whole population to clear asymptomatic infections and provide posttreatment prophylaxis to prevent reinfection. It has been used effectively in the control and elimination of diseases such as trachoma and in emergencies such as malaria epidemics. The use of MDA is recommended in areas approaching interruption of transmission; with good access to treatment, effective vector control, and surveillance systems; and having a minimal risk of reintroduction of infection [2]. MDAs have been conducted using a variety of drug regimens at different dosages, timings, and frequencies. These show substantial but short-lived reduction in *Plasmodium falciparum* parasite carriage [3]. With the growing awareness of heterogeneity and clustering in transmission, MDA approaches have been modified by systematic (mass screening and treatment) or focused (focal screening and treatment) screening and treatment of populations. Reactive case detection (i.e., screening treating positive contacts in response to a clinical event) has been tested [4, 5] and implemented in some countries [6, 7]. However, its impact has been variable [8, 9] because it is affected by the sensitivity of the diagnostic tool and the radius of intervention around a clinical case [10, 11]. These programs require strong coordination and often lack community engagement.

Malaria transmission in The Gambia is seasonal, occurring during and immediately after the rainy season (July–December), and has decreased significantly over the past decade [12, 13]. Key interventions that have led to this decline are case management with artemisinin-based combination therapy (ACT) and the use of long-lasting insecticidal nets (LLINs) [14]. Malaria case management involves screening suspected cases, mostly by a rapid diagnostic test (RDT), and treatment of positive cases with artemether-lumefantrine. This service is available at all public health facilities and from village health workers (VHWs) at the community level. VHWs are volunteers identified by their communities, trained by the government, and provided with RDTs and artemether-lumefantrine.

As malaria becomes uncommon, community engagement is needed to help identify cases or treat asymptomatic infected individuals, and these steps depend on a robust understanding of community perceptions of disease, infection, and transmission [15, 16]. The planned study develops and implements a strategy for community engagement to reduce malaria prevalence and thus malaria transmission. Such an approach of reactive treatment of clinical malaria cases’ contacts is developed using a mixed methods approach to understanding how communities perceive it and how it can be integrated within the existing health system.

### Trial objective

The objective of this trial is to determine whether administering an antimalarial treatment to all individuals living in the same compound of clinical malaria cases would result in a lower prevalence of *P. falciparum* infection at the village level.

## Methods/design

This is a cluster-randomized trial designed to assess the impact of reactive treatment of contacts of a clinical malaria case living in the same compound on the prevalence of malaria infection at the end of the transmission season. The trial is planned over two transmission seasons. In the first (exploratory) season, villages are identified and approaches to integrate the intervention into the community and health systems will be tested and adapted by social scientists and health systems researchers. The final portfolio of messages to support the intervention will be applied in the second (implementation) season (Fig. 1).

**Fig. 1 Fig1:**
[figure not shown]
Timeline for project activities

### Study setting

The study is being conducted in villages on the North Bank of the River Gambia and covers an area of approximately 45 km west of the town of Farafenni. *P. falciparum* is responsible for nearly all malaria infections in The Gambia [17]. Malaria transmission in this area has declined substantially, with parasite prevalence of about 3% in a population sampled during the peak of transmission [13]. It is therefore an ideal location because the intervention is designed for targeting residual clusters of transmission.

A village is composed of compounds, and each compound is clearly defined by a fence. It is typically composed of several buildings and rooms with different functions that serve one or several households. Locally, a household is defined as “all the people who eat from the same bowl” and consists of members of an extended patrilineal family. A typical compound has the men’s house, where each adult male has his own room; the women’s house, where the wives of all married men from the household, their daughters, and children stay; the kitchen; and the “boys’ house” for young circumcised men. The decision to treat all individuals in a compound was based on the need to cover as many individuals as possible around the clinical case and also because of the clear demarcation between compounds.

### Village selection and consenting

Medium-sized villages (population ≥ 100) in the area were targeted, and parasite prevalence by loop-mediated isothermal amplification (LAMP) assay was determined [18] in January 2016. Villages of this size were targeted because they are likely to have a resident VHW. Villages with a parasite prevalence > 0.5% were included in the trial and randomly assigned to an intervention or control arm using a computer-generated minimizing algorithm (Fig. 2). A census was conducted in each village to determine the population size and age structure. In addition, weight measurements were documented for residents in villages that made up the intervention arm.

**Fig. 2 Fig2:**
[figure not shown]
Village selection and randomization into trial arms

Because all residents of the villages are potentially at risk of infection and clinical malaria during the transmission season, a written informed consent will be required from everyone before study-related activities are implemented. To ease identification of compound members, consent will be obtained preemptively before the start of the malaria transmission season in all selected villages. Consent for children will be provided by their guardians, and those 12–17 years old will be asked to provide an assent in addition to a written consent from a responsible adult. This process will be updated in the course of the trial, especially in compounds where new residents have been added or individuals missed in the earlier exercise are reported. A list of residents in the study villages, by compound, including weight and consent status, will be generated and made available to study nurses at the local health facility and to VHWs involved in the trial.

### Activities in the intervention arm

Trial activities are initiated after an individual from a village assigned to intervention is diagnosed with malaria and treated at either a health facility or by a VHW with artemether-lumefantrine. Individuals living in the same compound as this index case will be identified from the census logbook produced for the trial, with the help of the patient or escort if the patient is a minor. A full (3-day) course of dihydroartemisinin-piperaquine (DP), dispensed on the basis of body weight, will be packed for each individual in the compound for distribution. DP is recommended for the treatment of uncomplicated *P. falciparum* malaria [19], available in pediatric (dihydroartemisinin 20 mg/piperaquine 160 mg) and older child/adult (dihydroartemisinin 40 mg/piperaquine 320 mg) tablet formulations, and administered as a once-daily treatment.

Where the clinical case is identified at a health facility, study nurses will hand treatment packs labeled with each recipient’s name and dosing instructions to the escort to take home. The study nurse informs the resident VHW or village collaborator (VC)—a volunteer identified by the community, if the village does not have a VHW—of the event and the compound where treatment has been sent. The VHW or VC then visits the compound on the same day and helps distribute the medicines. If the malaria case is detected by the VHW, he/she will visit the compound and distribute prepacked medicines to residents of the compound following instructions on the logbook developed in a way usable for VHWs. Follow-up visits will be scheduled for the day after treatment has been completed where the VHW or VC returns to the compound to confirm that treatment was taken, retrieve empty or unused drug packets, and inquire about any adverse events during the period. This information will be relayed back to the study nurse. A field assistant will collect any unused drugs and empty packets (Fig. 3).

**Fig. 3 Fig3:**
[figure not shown]
Schematic describing activities in the trial arms following identification of a malaria case

**Fig. 4 Fig4:**
[figure not shown]
Table showing schedule for enrollment, interventions, assessments, analysis, and dissemination of results

### Activities in the control arm

Activities in the control arm during the trial implementation period will be limited to observations of the routine case management of malaria by either the VHW or the health facility and measurement of the risk of infection in the compound of an index case. Where an index case is confirmed, it is reported to the study team that will visit the compound and collect a fingerprick blood sample for later detection of *P. falciparum* infection at the laboratory. Members of the compound are not treated.

### Eligibility and participation

The unique requirement for participation in the trial informs the need for an adaptive approach in the study design and defining eligibility. All residents in the intervention villages are potentially eligible. However, reactive treatment targets only compounds in the intervention villages where a clinical malaria case occurs and treats only compound members who are eligible at that time. The key eligibility criteria for receiving treatment include residence in the study area for at least 1 month during the transmission season, willingness to participate, weight ≥ 5 kg, and no known history of heart disease or allergies to DP; pregnant women are eligible only after the first trimester. Eligibility of compound members may change during the course of the trial period, so it is essential to ensure comprehension and maintain interest in the trial. For instance, pregnancy (first trimester) and weight (≥ 5 kg) status need to be confirmed at the time of treatment. Social scientists involved with the trial will explore perceptions of treatment for asymptomatic malaria infections and produce information that provides clarity and context to the trial activities, which will be shared with the communities during the implementation phase.

In the control arm, only a blood sample from the compound members will be collected. Therefore, the eligibility criteria are limited to residence in the study area for at least 1 month during the transmission season and willingness to participate.

### Study outcomes

The primary endpoint is the prevalence of *P. falciparum* malaria infection measured by molecular methods at the end of the second year. Prevalence will be compared between intervention and control arms.

Secondary endpoints include the following:Prevalence of clinical (laboratory-confirmed) malaria detected in study villages during the transmission seasonTreatment coverage: the proportion of individuals in each compound in the intervention arm that received and took the prescribed dosePrevalence of antimalarial drug resistance molecular markers and difference between study armsIn the control arm, the proportion of infected individuals at the time of a clinical event

### Sample size calculation

The sample size calculation assumed reactive treatment would result in a 60% difference in parasite prevalence between the intervention and control arms in an area with a prevalence around 5% [20]. A minimum of 16 villages per trial arm would be needed to detect such a reduction between the intervention and control arms with 80% power, a 5% significance level, and a coefficient of variation of 0.7 [21].

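### The 80% power for 16 villages per arm is worked out at a prevalence around 5%, but the protocol puts the study area at about 3%, where the same calculation falls short of 80%

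*Protocol article*

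**What the plan says.** Under Sample size calculation, the protocol article assumes a "60% difference in parasite prevalence between the intervention and control arms in an area with a prevalence around 5"%, with a citation for that prevalence. It then states: "A minimum of 16 villages per trial arm would be needed to detect such a reduction", "with 80% power, a 5% significance level, and a coefficient of variation of 0.7". It names neither the scale of the comparison nor the number tested per village, and does not say whether the 5% level is two-sided.

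Under Study setting, the same article describes the trial area as having "parasite prevalence of about 3% in a population sampled during the peak of transmission", again from a cited source, and uses this to support the choice of site. The assay behind that figure is not named.

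Under Village selection and consenting, villages of at least 100 residents were targeted, and those above 0.5% by LAMP in January 2016 were included. Under Data collection, management, and analysis, the primary endpoint is the proportion of sampled residents positive by varATS PCR, compared between arms with generalized estimating equations (GEE).

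**The concern.** The planning prevalence and the site prevalence differ by a factor of 5/3, and the article does not explain why the higher one was used. For a fixed relative reduction and a fixed coefficient of variation, lower prevalence leaves the between-village part of the variance unchanged relative to the effect, but it enlarges the sampling part. Power at 3% is therefore lower than at 5%.

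This is the article's only power statement for the primary endpoint. If power is lower than stated, a real 60% reduction is missed more often than the stated one time in five, and a null result could be over-read as evidence against reactive treatment.

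**Working it through.** **Inputs.** From Sample size calculation: 60% reduction, p0 = 0.05 and so p1 = 0.02, k = 0.7, power 80%, 16 villages per arm. From Study setting: p0 = 0.03, and so p1 = 0.012 at the same reduction. Assumed: two-sided 5%, so (1.96 + 0.84)² = 7.849; exactly 16 villages per arm; k unchanged at 3%. The number tested per village, m, is unknown and is solved for.

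**Formulas.** The scale is not stated, so two are used, each with and without the customary +1 village:

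- Difference scale: c = [+1] + 7.849 × {[p0(1−p0) + p1(1−p1)]/m + k²(p0² + p1²)} / (p0 − p1)²
- Log scale: c = [+1] + 7.849 × {2k² + (1−p0)/(m·p0) + (1−p1)/(m·p1)} / (ln 0.4)²

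**Numbers put in.**

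- Difference, 5%: 7.849 × 0.49 × 0.0029/0.0009 = 12.39, and 7.849 × 0.0671/0.0009 = 585. So c = [+1] + 12.39 + 585/m.
- Difference, 3%: the first term is again 12.39, and 7.849 × 0.040956/0.000324 = 992. So c = [+1] + 12.39 + 992/m.
- Log, 5%: 7.849 × 0.98/0.8396 = 9.16, and 7.849 × (19 + 49)/0.8396 = 636. So c = [+1] + 9.16 + 636/m.
- Log, 3%: 7.849 × (32.33 + 82.33)/0.8396 = 1072. So c = [+1] + 9.16 + 1072/m.

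**The plan's own figure.** Without m, 16 cannot be reproduced directly. It can be back-solved: 16 is the minimum at 5% when c lies above 15 and at or below 16. Carrying each such m to 3% with 16 villages, power = Φ(√[(16 − add)/V] − 1.96), where V is the c formula without the added village and without the factor 7.849, and add is 1 or 0.

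| Scale | m that makes 16 the minimum at 5% | Power at 3% with that m | m needed for 80% at 3% |
|---|---|---|---|
| Difference, no +1 | 163 to 224 | 74% to 78% | 276 |
| Difference, +1 | 225 to 364 | 75% to 79.7% | 381 |
| Log, no +1 | 93 to 108 | 69% to 73% | 157 |
| Log, +1 | 109 to 131 | 70% to 74% | 184 |

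**Why every row falls short.** Moving from 5% to 3% multiplies the m needed by 992/585 = 1.70 (difference) or 1072/636 = 1.69 (log). The slack from rounding up to a whole village is at most 364/225 = 1.62. No m for which 16 is the minimum at 5% is therefore enough at 3%.

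**Sidedness.** A one-sided 5% test does not rescue it. On the difference scale with +1, m = 90 gives c = 15.9 at 5% but 19.5 at 3%.

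**The case against.** The strongest reply is that 3% need not be the control-arm prevalence at the endpoint. It comes from an earlier sample by an unnamed assay. The endpoint uses a qPCR that the article describes as highly sensitive for low-density infections, and villages at or below 0.5% were left out. Both could bring control prevalence towards 5%. This stands as a caveat, but the article does not make the argument, and the reader has only the two unreconciled figures.

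Second, 16 is described as a minimum, and the number tested per village may be in the full protocol, which is not shown. If about 157-184 residents per village (log scale) or 276-381 (difference scale) are tested, 80% is reached at 3% with 16 villages. With 224 tested, the log scale gives 83-85% at 3%. This also stands, and it means that the trial's actual power is unknown from the article. What fails is the calculation as printed, carried to the site's own prevalence.

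Some stronger readings are tempting but unsupported:

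- *Power is only about 63%.* That figure assumes 3%, the difference scale and 100 tested in every village. The 100 is an entry floor, not a typical village size.
- *The 16 is an arithmetic error.* It is attainable at 5% with plausible numbers tested on either scale.
- *Leaving out the number tested is itself a defect.* An article may leave this to the full protocol.
- *The 0.5% entry rule or the survey date shows endpoint prevalence below 3%.* The entry rule removes low-prevalence villages. The final survey was planned for December, within the July-December transmission period, and nothing says that prevalence has dropped by then.

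**Conclusion.** The point holds, with moderate weight. The stated 80% power rests on a prevalence that the protocol's own site description does not support. At about 3%, any number tested per village consistent with 16 being the minimum at 5% gives about 69-80% power: 74-80% on the difference scale, where the best case is 79.7%, and 69-74% on the log scale. A true 60% reduction would then be missed in roughly 20-31% of such trials, against the stated 20%.

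This rests on a two-sided 5% test, exactly 16 villages per arm, a coefficient of variation of 0.7 at both prevalences, and 3% applying to the control arm at the endpoint. It does not show that the trial as run has less than 80% power. That depends on the villages enrolled, the residents tested and the prevalence by qPCR, none of which the article gives.

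**What to change.** Rewrite the sample size paragraph to:

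- give power at 3% as well as 5%, using the actual number of villages per arm and the number to be tested per village taken from the census already done;
- name the formula, the scale and the sidedness of the test;
- either justify 5% for varATS qPCR at the time of the final survey, or replace the 80% with the power at 3%, or with the reduction detectable at 80% power.

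No assumed number such as 100 per village should be written in. No extra villages are needed, and the endpoint, allocation and analysis do not change. The cost is one paragraph and, unless 5% can be justified or enough residents are tested, a slightly less favourable stated power.

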### Assignment of villages to trial arms

The unit of randomization is the village because the primary endpoint, malaria prevalence, is measured at this level. Using the data from a baseline survey in which blood samples were analyzed with a LAMP assay, the trial statistician will randomize villages to one of the two study arms using a computer-generated randomization sequence. First, a minimization algorithm [22] based on the imbalance measure by Raab and Butcher [23] will be used to generate a series of optimal scenarios that adjust for imbalances in prevalence between arms. Villages will then be randomly allocated, using a two-block randomization sequence, into two groups by selecting an optimal sequence from the lot generated. This will be done using Stata 14 software (StataCorp, College Station, TX, USA). Blinding of interventions is not feasible, because both individuals taking the medicines and health workers distributing them will be aware of who is receiving the intervention. However, samples collected during the study will be assigned unique identifiers, and staff processing samples will not be aware of the identity of the individuals or their allocation arm.

### Laboratory processes

Fingerprick blood samples collected on filter papers during the prevalence surveys and compound screening will be tested for *P. falciparum* infection by using a qPCR assay targeting the *var* gene acidic terminal sequence (varATS) [24]. This assay is highly sensitive and hence useful for the detection of low-density malaria infections that are usually found in low-transmission settings. Positive samples will be screened for molecular markers of drug resistance, namely the *Pfcrt*-76 and *Pfmdr1*-86 gene polymorphisms, using the established high-resolution melting protocols [25].

### Data collection, management, and analysis

Data from the census of the villages and measured weights will serve as the platform for trial activities and will be stored in a retrievable format in a Microsoft Access database (Microsoft Corp., Redmond, WA, USA) set up on electronic tablets. Information on the confirmed case will be used to identify the compound of the index case and generate a list of persons for treatment and follow-up. In the control villages, forms will be generated that are based on the compound of the malaria case for persons from whom to collect a blood sample for parasite detection. Completed forms will be double-entered into an OpenClinica database (OpenClinica LLC, Waltham MA, USA). Results derived from the analysis of samples from the prevalence surveys will be linked to the main trial database for the analysis. All staff involved in the trial will be trained on their specific tasks.

The primary endpoint, *P. falciparum* prevalence, defined as the proportion of sampled residents carrying parasites detectable by varATS PCR, will be compared between study arms using generalized estimating equations to account for within-cluster correlations. Random-effects multivariable logistic regression models will be used to analyze binary outcomes, and mixed linear regression will be used for normally distributed continuous outcomes. An interim analysis of results is not planned, and the analysis plan will be produced and agreed on before the close of the trial database.

For the cost-effectiveness analysis, we will describe the costing of the trial and estimate the costs of implementing similar interventions at a programmatic scale. This takes into account the existing infrastructure and a projection of any additional resources required to be able to deliver the interventions outside a trial setting and integrate them into the existing health system, including the National Malaria Control Program and community-based health services. We will run a series of sensitivity analyses, taking into account various possible inputs and processes for the interventions’ scaling-up (Fig. 4).

